**Fig. 1 Fig1:**
[figure not shown]
Overview of measures and measurement points. Abbreviations are explained by full name in Table 4

Treatment groups run through 2014–2016. The last follow up assessment is scheduled in December 2018. A detailed treatment manual for the new treatment method (PED-t) can be provided upon request. All treatment sessions are arranged at the Norwegian School of Sport Sciences in Oslo, Norway (NSSS).

### Inclusion and exclusion criteria

Included are women aged 18–40 years with a BMI in the range of 17.5–35, a DSM-5 diagnosis of BN or BED with duration of at least 3 months, and with mild to severe symptoms (minimum one episode per week of compensatory behaviors or binge eating, respectively) [41]. A signed letter from the women’s general practitioner (GP) confirming their suitability for the study is required for final enrollment.

Women not eligible are those who are or plan to become pregnant during the study period and those who are competitive athletes. Also excluded are those with a concurrent severe axis I and/or axis II mental disorder obviously in need of other treatments options not focusing on the ED. To prevent effect diffusions we also excluded individuals who have received CBT for ED during the last two years before the trial.

### Recruitment

Study- and contact information is distributed through GP’s, magazines and websites of the ED patient organizations, newspaper ads, national TV, social media, and posters.

Individuals calling by phone are informed about the project purpose, and for those who pass the inclusion criteria, a diagnostic screening is conducted using the Mini-International Neuropsychiatric Interview screening [42] and the Eating Disorder Examination (EDE-q) [41, 43, 44] (Fig. 2). Final inclusion is based on three written and signed declarations, *ie,* the informed consent by the woman to take part in the trial and the assessment procedures herein, a declaration of mutual secrecy about personal information revealed in the group treatment sessions, and a signed consent from their GP that they are medically fit to participate. These documents are returned personally upon the first visit to the NSSS.

**Fig. 2 Fig2:**
[figure not shown]
Recruitment, screening and randomization of participants

### Randomization

The participants complete the baseline measures before randomization. We use block randomization of size eight (https://www.randomizer.org/) to ensure equal sized treatment arms. A project-independent fellow worker allocated eligible participants to either treatment arm according to a concealed randomization list. Researchers and test personnel in the study are blind with regard to group allocation, but due to the nature of the two treatment procedures, therapists and participants are obviously not blinded to the treatment allocation. The participants are informed about their group allocation after completing the baseline measures.

### Safety procedures

A stop-procedure is activated if included subjects display a worsening of ED symptoms (eg. a BMI < 17.0 and/or rapid and significant weight loss of more than 3 kg from normal weight), severe depression or if severe osteoporosis is identified among those randomized to PED-t. Individuals excluded for any of these reasons are medically evaluated for admittance to health care services. Further: if participants report not to have been eating properly before exercise sessions in the PED-t groups, or if feeling ill, we tell the participant not to participate in the physical test or the exercise session that day. During the pre- and post-tests, if participants reports severe purging or restrictive eating in the days before, no physical tests will be performed. A defibrillator is available in the lab where physical tests are held, and a medical health care team is available next house if help is needed.

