**Methods:**

The PED-t trial uses a prospective randomized controlled design. It allocates women between 18 and 40 years (BMI range 17.5–35.0) to groups consisting of 5–8 members who receive either CBT or PED-t for 16 weeks. Excess participants are allocated to a waiting list control group condition. All participants are assessed at baseline, post-treatment, 6, 12 and 24 months’ post-follow-up, respectively, and monitored for changes in biological, psychological and therapy process variables. The primary outcome relates to the ED symptom severity, while secondary outcomes relates to treatment effects on physical health, treatment satisfaction, therapeutic alliance, and cost-effectiveness. We aim to disseminate the results in high-impact journals, preferable open access, and at international conferences.

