### Hypotheses and predictions

This trial will test six hypotheses:

1) Comparison of treatment arms: a) PED-t and CBT have comparable effects in terms of less symptoms of eating pathology, b) both perform better than a wait-list control group in reducing binge eating and/or purging, and c) both improve dietary intake.

2) Compared with CBT, the PED-t intervention produces a more rapid treatment response.

3) By improving physical strength and endurance, body composition, bone mass, and the nutritional and hormonal status, PED-t will surpass CBT in reducing the number and severity of medical complications.

4) Positive early changes in therapeutic alliance scores and group cohesiveness partly mediate effects of PED-t and CBT.

5) PED-t surpasses CBT in terms of a lower dropout rate and higher patient satisfaction with treatment.

6) The direct treatment costs are comparable for PED-t and CBT, but the indirect costs of PED-t are expected to be lower.

We predict that the PED-t combination will serve as an effective treatment method for BN and BED because the preoccupations of exercise and diets are transformed away from being ED-symptoms and toward functional coping and self-regulative activities. We also predict that the treatment effect of PED-t will be rapid and strong, defined according to a systematic review and meta-analysis [37], and the best empirically derived predictors of sustained remission at 6 and 12 months follow-up [38, 39] *ie*. as a 25% reduction in depression scores and ≤3 binge eating episodes a week during the first four weeks of treatment. Given that our novel treatment (PED-t) targets clinical features that occupy the sufferers’ minds, we expect a high level of treatment engagement, motivation and compliance. Such accomplishments may facilitate a stronger therapeutic alliance [40].

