### Statistical power and analyses

Analysis of covariance (ANCOVA) is used to raise statistical power. The effect size of the covariates is set to *R*
^*2*^ = 25%, alpha = .05 and 1-beta = .80. The CBT treatment effect for EDs using the Eating Disorder Examination Questionnaire is about *d* = 1.30 [45]. A small change (*d* = 0.30) in the wait-list condition requires 14 subjects in each group (total *N* = 28), but since the difference between the PED-t and CBT treatment conditions is of primary interest a non-inferiority margin of *d* = 0.45 is considered as clinically relevant [46]. This requires a sample size of 62 + 62 subjects, increasing to 72 + 72 when adjusting for the group therapy factor (intra-class correlation = .05, design factor 1.16). The longitudinal data will be analyzed using multilevel regression models to accommodate for dependency in the repeated data within subjects and within groups. The maximum likelihood procedure uses all information available, thus, handling dropout well. Multiple imputation will be used to impute missing values. Follow-up data is analyzed with mixed model regression to estimate correct between-group treatment effects adjusted for within-group variance components related to patients and groups. Moderator variables will be included to analyze whether any treatment effects are modified by variables as motivation, therapist alliance or group cohesiveness. If treatment arms do not differ in outcome, combined latent class growth curve modeling will be conducted to analyze reasons for individual differences at startup and in the rate of change across time.

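### Stopped participants are called excluded, and the osteoporosis trigger applies to PED-t only; if they leave assessment or analysis, the arm comparisons can be biased

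*Protocol article*

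**What the plan says.** All references are to the protocol article.

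- **Safety procedures.** The rule starts with symptoms: "A stop-procedure is activated if included subjects display a worsening of ED symptoms". The examples given are weight-based (BMI below 17.0, or rapid loss of more than 3 kg). It then adds "severe depression or if severe osteoporosis is identified among those randomized to PED-t". The status of these women is given once: "Individuals excluded for any of these reasons are medically evaluated for admittance to health care services". A separate rule covers the pre- and post-tests: "if participants reports severe purging or restrictive eating in the days before, no physical tests will be performed".
- **Randomization.** "The participants complete the baseline measures before randomization". Methods and design schedules every outcome at pre, post, 6, 12 and 24 months, and Measures and variables includes bone density by DXA. Bone status is therefore known in both arms before allocation. Osteoporosis is not among the inclusion and exclusion criteria.
- **Outcomes.** In the Abstract, "The primary outcome relates to the ED symptom severity". Hypothesis 3 reads "By improving physical strength and endurance, body composition, bone mass, and the nutritional and hormonal status, PED-t will surpass CBT" in reducing medical complications. Hypothesis 5 expects less dropout in PED-t.
- **Statistical power and analyses.** "The maximum likelihood procedure uses all information available, thus, handling dropout well". Multiple imputation is also planned. The end of Measures and variables adds a comparison of leavers with continuers on pretest values.

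**The concern.** Three features act together. The stop happens after randomisation. One trigger lies in the same domain as the primary outcome. Another trigger exists in one arm only.

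If *excluded* means that no further outcomes are collected, or that the woman is left out of the analysis, the arms compared are no longer the arms randomised:

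- **Hypothesis 3.** Women with very poor bone status leave PED-t, while comparable women stay in CBT. Hypothesis 3 also concerns the number and severity of medical complications, so the same rule takes such cases out of one arm.
- **Hypothesis 5.** Osteoporosis stops count as PED-t exits, and CBT has no equivalent.
- **Hypothesis 1a.** The arm with more harm-triggered stops loses more of its worst outcomes and looks better. If that arm is PED-t, the error favours a non-inferiority conclusion.

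The two stated safeguards do not cover this. Maximum likelihood and multiple imputation rest on observed data. A stop driven by worsening between the pre and post visits is covered only if that worsening is recorded and used. The pretest comparison cannot show loss that depends on change after baseline.

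**Working it through.** **1. The scale of the margin.** The article gives a margin of d = 0.45, alpha .05 and power .80. With one-sided alpha .05 and no covariate gain, n = 2(1.645 + 0.842)²/0.45² = 61.1, so 62 per arm. Then 62 × 1.16 = 71.9, so 72. The stated sizes reproduce on this basis (the article does not state sidedness), so biases below are set against 0.45 SD with 72 per arm.

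**2. Stop rates.** The article gives none. All shares below are assumptions. Of 72 women, 5%, 10%, 15% and 20% are 3.6, 7.2, 10.8 and 14.4.

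**3. Hypothesis 1a, symptom-triggered stops.** Simulation with 300,000 per arm and a true difference of 0. Baseline, mid-treatment and post scores have SD 1. Baseline correlates .5 with each later score. Given baseline, the mid and post scores correlate .5, .7 or .9. The women with the largest rise from baseline to mid-treatment are removed and their post score is missing. Estimates come from ANCOVA on baseline; negative values favour PED-t.

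| Removed, PED-t / CBT | Trigger not modelled (.5 / .7 / .9) |
|---|---|
| 5% / 5% | 0.001 / 0.002 / −0.001 |
| 10% / 10% | −0.002 / 0.005 / 0.001 |
| 10% / 5% | −0.037 / −0.050 / −0.065 |
| 15% / 5% | −0.067 / −0.093 / −0.122 |
| 20% / 5% | −0.101 / −0.136 / −0.175 |

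As a share of the margin, the unequal rows run from 0.037/0.45 = 8% to 0.175/0.45 = 39%. When the mid-treatment score is used to impute the missing post score, the bias is within 0.005 of zero in every row. If CBT lost more, the sign would reverse.

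**4. Primary outcome, osteoporosis rule alone.** If a fraction f of PED-t is removed and would have scored s SD worse than those kept, the arm mean shifts by f × s. With f = 1–2% and s = 0.5–1.0, the shift is 0.01 × 0.5 = 0.005 to 0.02 × 1.0 = 0.02 d.

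**5. Hypothesis 3, bone density.** Removing the lowest fraction x of a normal distribution raises the mean by φ(z)/(1 − x). For x = 1%: 0.0267/0.99 = 0.027 SD. For x = 2%: 0.0484/0.98 = 0.049 SD. These are unadjusted shifts. If the stop follows from the baseline scan and the model adjusts for baseline bone density, loss depends on an observed value in the model and most of the shift goes.

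**6. Hypothesis 5.** At 1–2% of 72, the rule adds 0.7 to 1.4 PED-t exits, or 1 to 2 percentage points, with no counterpart in CBT.

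**The case against.** The strongest reply is that loss from assessment is assumed. The article describes a stop procedure and a medical evaluation. It does not say that follow-up ends or data are discarded, and the five-visit schedule names no exception. The full protocol or analysis plan may settle this. That stands, and it makes the bias conditional. It does not dispose of the point: *excluded* is the only status the text gives these women, the one-arm trigger is explicit, and the assurance about dropout is given without qualification.

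A reader might infer more than the documents support:

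- **That the comparison is biased.** The symptom and depression triggers read as applying to all included subjects, and equal removal gives a bias of about 0.
- **That women are removed for a poor primary score.** The examples are BMI and weight loss, not the EDE-q. The overlap is of domain only.
- **That the missing-data assumption is broken.** Likelihood and imputation methods remain valid if the trigger is observed and modelled. Weekly weigh-ins are planned and could serve for the weight triggers. The weakness is that nothing stated ties such data to the analysis.
- **That the osteoporosis rule distorts hypothesis 3 whatever the analysis.** ANCOVA is planned, and adjustment for baseline bone density would remove most of it. The article does not say that this is the covariate.
- **That skipped physical tests are permanently missing.** That rule covers both arms, and nothing says a test cannot be done later.

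**Conclusion.** The point holds in conditional form and deserves a correction. As written, the safety rule creates a post-randomisation exclusion that depends on arm through osteoporosis, on a variable known in both arms before allocation. Neither the statement on maximum likelihood nor the pretest comparison covers it.

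The consequences depend on stopped women leaving assessment or analysis, which the wording suggests but does not state. Hypotheses 3 and 5 are affected most directly, modestly if few women meet the criterion. For hypothesis 1a the risk comes from unequal symptom or depression stops with the trigger left out of the model. Its size there rests on assumed stop rates: nil if equal, and up to about two fifths of the margin at the extreme assumed imbalance of 20% against 5%. The osteoporosis rule by itself is negligible for the primary outcome. No view is taken on the clinical stopping criteria.

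**What to change.** Leave the clinical stop rule as it is and add the following:

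1. State that stopping treatment is not leaving the study. Keep stopped participants in the scheduled outcome assessments and in the analysis as randomised.
2. Record the reason for each stop and report stops by arm. For hypothesis 5, count protocol stops separately from voluntary dropout.
3. For hypothesis 3, adjust for baseline bone density and, in the analysis, treat women who meet the osteoporosis criterion at baseline identically in both arms.
4. Put the trigger data in the imputation model: weekly weight, depression score, and EDE-q purging and restriction.
5. Add one sensitivity analysis that imputes stopped participants as worse than the main model predicts.
6. Qualify the sentence on dropout: the method is adequate for these exits only to the extent that their causes are observed and modelled.

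The cost is follow-up of probably a few stopped participants, a log of stop reasons and slightly more analysis work. The sample size does not change.

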### Statistical power and analyses

Analysis of covariance (ANCOVA) is used to raise statistical power. The effect size of the covariates is set to *R*
^*2*^ = 25%, alpha = .05 and 1-beta = .80. The CBT treatment effect for EDs using the Eating Disorder Examination Questionnaire is about *d* = 1.30 [45]. A small change (*d* = 0.30) in the wait-list condition requires 14 subjects in each group (total *N* = 28), but since the difference between the PED-t and CBT treatment conditions is of primary interest a non-inferiority margin of *d* = 0.45 is considered as clinically relevant [46]. This requires a sample size of 62 + 62 subjects, increasing to 72 + 72 when adjusting for the group therapy factor (intra-class correlation = .05, design factor 1.16). The longitudinal data will be analyzed using multilevel regression models to accommodate for dependency in the repeated data within subjects and within groups. The maximum likelihood procedure uses all information available, thus, handling dropout well. Multiple imputation will be used to impute missing values. Follow-up data is analyzed with mixed model regression to estimate correct between-group treatment effects adjusted for within-group variance components related to patients and groups. Moderator variables will be included to analyze whether any treatment effects are modified by variables as motivation, therapist alliance or group cohesiveness. If treatment arms do not differ in outcome, combined latent class growth curve modeling will be conducted to analyze reasons for individual differences at startup and in the rate of change across time.

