## Background

The present paper reports on an ongoing, new treatment for bulimia nervosa (BN) and binge eating disorders (BED). Binge eating disrupts normal eating patterns and introduces vicious circles of fasting and binging that causes a chaotic energy intake. Also, binge eating causes an energy surplus, which those with BN compensate for by purging, *eg.* vomiting, using laxatives, diuretics, or enemas, misusing medications or exercising in an extreme or rigid manner, all which can change body metabolism. It is noteworthy that such changes may also be the result of physical inactivity, which is frequently observed particularly among sufferers from BED.

Binge eating and compensatory behaviors can raise the medical severity of BN and BED by means of hypokalemia, that may elicit inter-current infections as well as cardiac complications, diseases or arrest, or it may affect glucose, insulin and lipid levels that increases the risk of type-2 diabetes [1–5]. A combination of rigid exercising and eating may over time inflict chronic low energy availability and raise the risk for low bone mineral density, and ultimately osteoporosis [6, 7]. The non-medical severity comprises personal and familial burdens. A slightly raised standardized mortality rate is due to both medical and non-medical burdens [8–10]. According to a recent systematic review, the societal health care costs range from €888–18,283 for BN and €1762–2902 for BED [8–10].

Most sufferers do not acknowledge the clinical severity and the medical and non-medical risks of eating disorders (ED), as 80–94% of people with BN and BED never seek professional help or delay it 4–5 years [11–15]. Effective treatment of BN and BED is considerably hampered by this incongruence, which may be circumvented by offering treatment options outside the contexts of traditional health services or improving access to such options. Among those who do enter treatment, a protracted course of illness is typically seen among every third patient [16]. Important reasons are early drop-out due to a failure to engage patients into treatment and lack of rapid symptom changes or symptom coping, thereby lowering patients’ motivation and self-efficacy [17].

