## Methods and design

This randomized controlled trial includes three groups: participants are randomized to either the CBT or the PED-t treatment group, while participants having to wait represent the control group condition. After 16–20 weeks, these are randomized to either treatment arm. The treatments are delivered to groups consisting of 5–8 participants. It includes 20 therapy sessions stretching across 16 weeks. All outcome variables are measured five times: pre, post, 6, 12 and 24 months (Fig. 1). Mediator/moderator data (*ie*. therapy process variables) are collected after each treatment session, which yields excellent statistical power for conducting growth curve modeling, nuanced mediation or moderation analyses.

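### The design factor of 1.16 is not the design effect for an intra-class correlation of .05 and therapy groups of 5–8; the correct range is 1.20–1.35, and the power at 72 + 72 should be restated

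*Protocol article*

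**What the plan says.** In the protocol article, Statistical power and analyses, ANCOVA "is used to raise statistical power". The covariate R² is set together with the error rates: "25%, alpha = .05 and 1-beta = .80". For PED-t against CBT, "a non-inferiority margin of *d* = 0.45 is considered as clinically relevant". The number before any allowance for clustering is then given: "This requires a sample size of 62 + 62 subjects". The allowance for treatment in groups comes next, with its two ingredients in brackets: "increasing to 72 + 72 when adjusting for the group therapy factor (intra-class correlation = .05, design factor 1.16".

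Methods and design gives the cluster size: "The treatments are delivered to groups consisting of 5–8 participants". The abstract gives the same range.

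The article does not say which group size lies behind 1.16, whether alpha is one-sided, or whether the R² of 25% is already contained in the 62.

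**The concern.** The step from 62 to 72 rests on a single multiplier. That multiplier is fully determined by the intra-class correlation and the therapy group size, both of which the article states, and the three figures do not agree: no group size from 5 to 8 yields 1.16 at a correlation of .05.

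This matters because the calculation sizes the main comparison between the two active treatments. If clustering is under-counted at the planning stage, the confidence interval for the treatment difference will be wider than planned. A non-inferiority trial is then more likely to end inconclusively, and readers would judge such a result against a stated power of 80%.

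**Working it through.** **Inputs.** Margin d = 0.45, alpha .05, power .80, R² = 25%, 62 per arm before and 72 after clustering, intra-class correlation .05 and factor 1.16 (all from Statistical power and analyses); group size m = 5–8, midpoint 6.5 (Methods and design). Assumptions: true difference zero, equal arms, SD of 1.

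**Step 1: reproduce 62.** n per arm = 2 × ((z for 1 − alpha + z for power) / 0.45)². At one-sided .05 without R², this is 2 × (2.486 / 0.45)² = 61.06, so 62. A t-based calculation also gives 62 (power .801 at 62, .796 at 61). The alternatives do not fit:

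- one-sided .025 without R²: 78 (t-based 79)
- one-sided .05 with R² = .25: 46 (t-based 47)
- one-sided .025 with R² = .25: 59 (t-based 60)

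The 14 per group for the wait-list contrast (d = 1.30 − 0.30 = 1.0) is likewise the t-based result at one-sided .05 without R². R² therefore does not seem to be in the 62, although the article does not say so.

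**Step 2: reproduce 72.** 62 × 1.16 = 71.92, rounded up to 72.

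**Step 3: check the factor.** Design effect = 1 + (m − 1) × ICC. Solving for 1.16: m = 1 + 0.16 / 0.05 = 4.2, below the smallest planned group.

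**Step 4: apply the correct factor.** Power is by noncentral t on the basis that reproduces 62, with effective n = 72 / design effect.

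| m | Design effect | 62 × design effect | Needed per arm | Effective n at 72 | Power at 72 |
|---|---|---|---|---|---|
| 5 | 1.20 | 74.4 | 75 | 60.0 | 79.0% |
| 6.5 | 1.275 | 79.05 | 80 | 56.5 | 76.8% |
| 8 | 1.35 | 83.7 | 84 | 53.3 | 74.7% |

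**Step 5: credit R² = 25%.** The margin is divided by √0.75, and the same design effects are kept.

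| m | Power at 72, one-sided .05 | Power at 72, one-sided .025 |
|---|---|---|
| 5 | 88% | 81% |
| 6.5 | 86% | 78% |
| 8 | 85% | 76% |

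**Sensitivity.** If degrees of freedom come from the number of therapy groups (72 / m, about 9–14 per arm), power for m = 5, 6.5 and 8 is 78%, 75% and 72% without R² at one-sided .05. With R² it is 87%, 85% and 82% at one-sided .05, and 78%, 75% and 71% at one-sided .025.

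**Possible origin (an inference).** √(1 + 7 × .05) = √1.35 = 1.162, which is the square root of the design effect for groups of 8. That quantity inflates a standard error; n has to be multiplied by its square, 1.35.

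**The case against.** The strongest counter-argument is that the article names R² = 25% as a design input. If it is credited at one-sided .05, 72 per arm exceeds 80% power even at the correct design effect for groups of 8. This stands. A reader might infer from the wrong factor that the trial is underpowered outright, but the article does not support that: it fixes neither the sidedness of alpha nor the role of R² in this calculation. The objection does not rescue 1.16 itself, since a covariate gain does not alter the relation between group size, intra-class correlation and design effect.

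Three further inferences are tempting but unsupported.

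- **Block size as the source.** Randomization says "We use block randomization of size eight", so one might trace 1.16 to four participants per arm in each block. Four gives 1 + 3 × .05 = 1.15, not 1.16. It is true that 62 × 1.15 = 71.3 also rounds up to 72, so the 72 alone does not identify the factor; but the article prints 1.16.
- **Missing dropout allowance.** The Background says, of the protracted illness seen in treated patients, "Important reasons are early drop-out due to a failure to engage patients into treatment". That describes patients in general and forecasts nothing for this trial. A condensed article may also leave a dropout allowance to the full protocol, so its absence is not counted here.
- **Invalid analysis.** The planned multilevel models include variance components for patients and groups. Clustering is under-counted in planning only, and the type I error is not at stake.

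**Conclusion.** The printed design factor is wrong for the stated intra-class correlation and group sizes, and this part does not depend on any assumption about sidedness or covariates. On the article's own base, 72 per arm is 3, 8 or 12 short of the number needed for groups of 5, 6.5 or 8.

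The effect on power is modest and conditional. On the only one of the four bases tried that reproduces 62, the loss against 80% is about 1, 3 or 5 percentage points. It disappears if R² = 25% is achieved and alpha is one-sided .05. At one-sided .025 with R², power sits from just above to about 4 points below 80%. These figures assume a true difference of zero, an intra-class correlation of .05 in both arms, equal group sizes and no loss to follow-up.

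This is a planning figure to be corrected. It does not threaten the validity of the trial.

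**What to change.** In Statistical power and analyses, replace 1.16 by 1 + (mean group size − 1) × .05, using the planned or realised mean group size (1.275 at 6.5; range 1.20–1.35). Keep 72 + 72 and restate the power it delivers. In the same sentence, say whether alpha is one-sided .05 or .025 and whether the R² of 25% is included.

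The cost is one corrected sentence and, on the basis that reproduces 62, a slightly less favourable stated power. No extra enrolment and no change to the analysis are needed.
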